### Intervention

Interventions will start once patients are hemodynamically stable (typically within 1–2 days post-surgery, usually on postoperative day 2) and will continue for 10 consecutive days during Phase I cardiac rehabilitation. Each session will last 10–15 minutes, conducted twice daily, with exercise progression based on vital stability and patient tolerance. The intervention protocol follows the American Heart Association and ACSM guidelines for early mobilization after cardiac surgery. All sessions will be supervised by certified physiotherapists trained in Phase I cardiac rehabilitation, using standardized checklists to ensure fidelity. Session adherence will be documented daily in participant logbooks. Safety parameters, including heart rate, blood pressure, oxygen saturation (SpO₂), and ECG (when available), will be continuously monitored. Exercise sessions will be immediately terminated in the event of chest pain, SpO₂ <90%, heart rate >120 bpm, arrhythmia, dizziness, or excessive fatigue. Outcome assessors will remain blinded to group allocation to minimize measurement bias.

Any adverse event or serious adverse event (e.g. hypotension, syncope, or wound bleeding) occurring during or after exercise sessions will be documented and reported to the institutional safety committee within 24 hours. Emergency medical support will be available on-site during all sessions.

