### Experimental group: (leg cycle ergometry + conventional physiotherapy)

Participants in the experimental group will receive a structured 10-day rehabilitation program combining leg cycle ergometry with conventional physiotherapy. This protocol was modified from Faizan Hamid et al. [10] and Guida et al. (2020).

Initial sessions emphasize breathing control and gentle mobilization to promote circulation and respiratory efficiency. Leg cycle ergometry will begin on day 2 and increase gradually to 15 minutes by day 10, performed twice daily with continuous monitoring. Ambulation, chair transfers, and stepper training are progressively added to enhance lower-limb strength, venous return, and cardiorespiratory endurance. All ergometer sessions will be supervised by the same physiotherapist to ensure uniform progression and adherence.

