### Control group

Participants in the control group will follow a 10-day progressive mobilization program based on standard Phase I cardiac rehabilitation [14, 15].

Sessions include diaphragmatic breathing, active limb mobility, chair transfers, stepper training, and ambulation, each performed twice daily for 10–15 minutes per session. Exercise progression will depend on patient tolerance and vital stability (SpO₂ ≥94%, HR ≤110 bpm, Borg RPE ≤13).

Sessions will be conducted under the same supervision and safety monitoring as the experimental group to ensure protocol fidelity.

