#### Group A: experimental group (leg cycle ergometry + conventional physiotherapy)[16]

Participants will undergo a 10-day structured exercise program. Each session lasts 10–15 minutes, twice daily, continuously monitoring vital signs. Exercise progression is based on patient tolerance, as detailed in Table 1.

**Table 1 Tab1:** Day-wise structured protocol for Experimental Group

**Day**	**Exercise protocol**	**Patient position/rationale**
1	• Breathing exercises (1 set of 10 reps) • Active upper and lower limb mobility (1 set of 10 reps)	Supine, head of bed 45° – improve venous return and prevent orthostatic stress
2	• Breathing exercises (1 set of 10 reps) • Active upper and lower limb mobility (1 set of 10 reps) • Standing upright and on-the-spot walking (2 x 1 min) • Leg cycle ergometry (2min)	Supine for ergometer, supported standing for walk – early mobility, circulation
3	• Breathing exercises (1 set of 10 reps) • Active upper and lower limb mobility (1 set of 10 reps) • Standing upright and on-the-spot walking (2 x 1 min) • Ambulation around bed (2-3min) • Leg cycle ergometry(5min)	Edge of bed sitting for chair transfer, supine on ergometer to strengthen lower limbs and functional mobility
4	• Breathing exercises (1 set of 10 reps) • Active upper and lower limb mobility (1 set of 10 reps) • Standing upright and on-the-spot walking (2 x 1 min) • Ambulation around bed (2-3min) • Chair transfer (15min) • Leg cycle ergometry (5min)	Positions same as Day 3. Gradually increasing duration to improve endurance
5	• Breathing exercises (1 set of 10 reps) • Active upper and lower limb mobility (1 set of 10 reps) • Standing upright and on-the-spot walking (2 x 1 min) • Ambulation (15min) • Chair transfer (10-15min) • Leg cycle ergometry (10min)	Focus on progressive functional recovery
6	• Active mobility exercise • Ambulation (10-15min) • Step training on stepper (3–5 min x 2) • Leg cycle ergometry (10 min)	Standing/semi-standing for stepper, supine/seated for ergometer, to improve lower limb strength balance and cardiorespiratory fitness.
7	• Active mobility exercises • Ambulation (10–15 min) • Leg cycle ergometry (10min)	Maintain progressive intensity and endurance.
8	• Active mobility exercises • Stepper training (3–5 min x 2) • Leg cycle ergometry (15 min)	Resistance and ergometer exercise enhance muscle strength and functional capacity

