9	• Active mobility exercises • Stepper training (3-5min x 2) • Leg cycle ergometry (15 min)	Resistance and ergometer exercise enhance muscle strength and functional capacity
10	• Active mobility exercise • Stepper training (3-5min x 2) • Leg cycle ergometry (15 min)	Resistance and ergometer exercise enhance muscle strength and functional capacity

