#### Group B: control group (conventional physiotherapy)

Participants follow a 10-day progressive mobilization program without leg cycle ergometry. Exercise selection is based on published Phase I cardiac rehabilitation guidelines detailed in Table 2. (Supplementary 2).

**Table 2. Tab2:** Day-wise structured protocol for Control Group

Day	Exercise Protocol	Patient Position/Rationale
1	• Diaphragmatic breathing (1 set of 10 reps) • Active upper and lower limb mobility (1 set of 10 reps)	Supine, head-of-bed elevated 45° improve circulation, respiratory function
2	• Diaphragmatic breathing (1 set of 10 reps) • Active upper and lower limb mobility (1 set of 10 reps) • Standing upright and on-the-spot walking (2 x 1 min)	Standing with support; early ambulation promotes functional recovery
3	• Diaphragmatic breathing (1 set of 10 reps) • Active upper and lower limb mobility (1 set of 10 reps) • Standing upright and on-the-spot walking (2 x 1 min) • Ambulation around the ward (5 min) • Chair transfer (2 min)	Edge-of-bed sitting, standing for ambulation; improve independence
4	• Diaphragmatic breathing (1 set of 10 reps) • Active upper and lower limb mobility (1 set of 10 reps) • Standing upright and on-the-spot walking (2 x 1 min) • Ambulation around the ward (5 min) • Chair Transfer (5min)	Progressive increase in duration to enhance endurance
5	• Diaphragmatic breathing (1 set of 10 reps) • Active upper and lower limb mobility (1 set of 10 reps) • Standing upright and on-the-spot walking (2 x 1 min) • Ambulation (15 min) • Chair transfer (10 min)	Focus on functional mobility
6	• Active mobility exercises • Step training on the stepper (2 x daily) • Chair transfer (10 min)	Standing/semi-standing; improve lower limb strength and balance
7	• Active mobility exercise • Step training (2 x daily) • Chair transfer (15 min)	Maintain intensity and improve confidence in movement
8	• Active mobility exercises • Stepper training (2 x daily) • Resistance exercises (2 x 10 min)	Strengthening the lower limb and functional independence
9	• Active mobility exercise • Stepper training (2 x daily) • Resistance exercises (2 x 10 min)	Progressive overload for strength
10	• Active mobility exercises • Stepper training (2 x daily) • Resistance exercise (2 x 10 min)	Progressive overload for functional gains

Exercises will be paused or discontinued if any adverse symptoms appear, and patients will be re-evaluated before resuming activity.

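### Experimental arm: the stated session of 10–15 minutes twice daily does not fit the day-wise exercise table, so total ergometry is 87 or 174 minutes depending on how a row is read

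*Protocol article*

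**What the plan says.** The Intervention section of the protocol article applies one session length to both arms: "Each session will last 10–15 minutes, conducted twice daily, with exercise progression based on vital stability and patient tolerance". The paragraph above Table 1 repeats it for the experimental arm, "Each session lasts 10–15 minutes, twice daily, continuously monitoring vital signs", and refers to Table 1 for the detail of progression.

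The Experimental group section adds an ergometry schedule: "Leg cycle ergometry will begin on day 2 and increase gradually to 15 minutes by day 10, performed twice daily with continuous monitoring". The Control group section lists that arm's exercises and then says "each performed twice daily for 10–15 minutes per session".

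Table 1 gives minutes for most items. Examples are "Chair transfer (15min) • Leg cycle ergometry (5min" on day 4, "Ambulation (15min) • Chair transfer (10-15min) • Leg cycle ergometry (10min" on day 5 and "Stepper training (3-5min x 2) • Leg cycle ergometry (15 min" on days 9 and 10. Table 2 mixes plain minutes, a stepper entry given only as a frequency per day, and "Resistance exercises (2 x 10 min". Neither table says whether a row is one session or a whole day.

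**The concern.** Ergometry is the only component that the trial means to test, as an addition to conventional physiotherapy. Its dose should therefore be readable from the protocol without a choice of interpretation. Here the session length, the frequency and the daily content are all printed, and they disagree. A therapist working to the session length and one working to the table row could deliver different amounts of exercise, both in good faith. A reader of the results could not tell which dose produced them. The Trial status section gives recruitment as starting in June 2025 under version 1.0 with no amendments, so patients may already have been treated under differing readings.

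**Working it through.** **Inputs.** The limits come from the Intervention section: at most 15 minutes per session and 2 × 15 = 30 minutes per day. Item times come from Tables 1 and 2. Breathing and limb-mobility sets have no times and are counted as zero, which favours the plan.

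**Experimental arm, sum of timed items per row (minutes)**

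| Day | Sum | Row = one session (limit 15) | Row = whole day, halved (limit 15) |
|---|---|---|---|
| 1 | none timed | fits | fits |
| 2 | 2 + 2 = 4 | fits | 2 |
| 3 | 2 + (2–3) + 5 = 9–10 | fits | 4.5–5 |
| 4 | 2 + (2–3) + 15 + 5 = 24–25 | exceeds | 12–12.5 |
| 5 | 2 + 15 + (10–15) + 10 = 37–42 | exceeds | 18.5–21, exceeds |
| 6 | (10–15) + (6–10) + 10 = 26–35 | exceeds | 13–17.5, upper end exceeds |
| 7 | (10–15) + 10 = 20–25 | exceeds | 10–12.5 |
| 8–10 | (6–10) + 15 = 21–25 | exceeds | 10.5–12.5 |

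**Reading 1: a row is one session.** Seven of ten days exceed 15 minutes. If each doubled entry (on-the-spot walking and stepper) means one bout in each of two sessions, the sums become 23–24 (day 4), 36–41 (day 5), 23–30 (day 6), 20–25 (day 7) and 18–20 (days 8 to 10). All still exceed 15. On days 8 to 10 ergometry alone takes the full 15 minutes.

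**Reading 2: a row is a daily total.** Day 5 exceeds 30 minutes throughout its range, and day 6 does so at its upper end. The Experimental group section, taken at face value, gives 15 minutes of ergometry twice daily. On days 8 to 10 that is 2 × 15 = 30 minutes, the whole daily maximum, with stepper and mobility work still listed.

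**Reading 3: the 10–15 minutes applies to each exercise.** The Control group wording allows this, and no single timed item exceeds 15 minutes. But the Intervention section and the paragraph above Table 1 attach the figure to the session. Several entries also fall below 10 minutes: ergometry of 2 and 5 minutes (Table 1, days 2 to 4), and chair transfer of 2 and 5 minutes and ambulation of 5 minutes (Table 2, days 3 and 4).

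**Control arm.** As single sessions, day 5 is 2 + 15 + 10 = 27 minutes. Days 8 to 10 are 20 minutes if both 10-minute resistance bouts fall in one session. Day 7 is exactly 15 before the untimed stepper. As daily totals the timed items fit: 27 / 2 = 13.5 minutes per session on day 5 and 20 / 2 = 10 on days 8 to 10.

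**Total ergometry, days 2 to 10.** 2 + 5 + 5 + 10 + 10 + 10 + 15 + 15 + 15 = 87 minutes if rows are daily. If rows are per session and done twice daily, 2 × 87 = 174 minutes.

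**The case against.** The strongest reply is that the two-fold spread rests on a reading that the Experimental group section itself counts against. If ergometry is given twice daily, the frequency is settled and 174 stands. That is the more natural reading of that section, but it makes the session length fail on days 4 to 10. The daily reading keeps the session length on most days but strains that section. Neither agrees with the whole text, so the spread stands as a measure of the ambiguity.

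Other replies have some force. Progression depends on tolerance and vital signs, so the tables are not rigid. However, tolerance does not say whether a row is a session or a day. One physiotherapist supervises all ergometer sessions, which should limit variation between therapists, but it does not tell a reader which dose was given. The day 4 excess comes entirely from the 15-minute chair transfer; without it the row is 9–10 minutes. Leaving chair transfer out on day 5 still gives 2 + 15 + 10 = 27 minutes.

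A reader might infer several stronger things that the documents do not support:

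- **Both arms equally contradict their tables.** The control arm's timed items fit as daily totals.
- **Patients generally receive nearly three times the stated session.** The ratio 42 / 15 = 2.8 is the upper end of one day under one reading.
- **Days 8 to 10 become ergometry alone.** Nothing says that a therapist would drop the other items.
- **Fidelity cannot be scored.** The article provides checklists and logbooks and cites a supplement. These are not shown and may define the unit.

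**Conclusion.** The plan is wrong as written for the experimental arm: the stated session length conflicts with the trial's own schedule. As sessions, rows exceed 15 minutes on seven of ten days. As daily totals, day 5 fails outright and day 6 can fail. Applying the figure to each exercise removes the upper-limit breach but contradicts the wording on sessions and the short table entries. Days 1 to 3 fit in both arms. For the control arm the finding is limited to mixed units and to day 5, possibly days 8 to 10, if rows are sessions.

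The consequence is that programme ergometry is 87 or 174 minutes, and the article does not settle which. This assumes zero time for untimed items and takes the printed minutes at face value. Randomisation and blinded assessment are not affected; what is unclear is the intervention being compared.

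**What to change.** The investigators should reconcile the Intervention, Experimental group and Control group sections with the Group A and Group B sections and Tables 1 and 2. The amended text should state:

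- whether a table row is one session or a whole day;
- whether the 10–15 minutes applies to the session, to each exercise or to ergometry only;
- one unit throughout both tables, including the doubled and per-day entries.

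Whether the text or the tables carry the intended dose is for the investigators to decide, and nothing here favours either. Adherence logs and fidelity checklists should then use the reconciled target. Patients already treated should be flagged by the version applied to them.

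The cost is a protocol amendment and a re-briefing of therapists. No extra patients or procedures are needed.

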### Experimental group: (leg cycle ergometry + conventional physiotherapy)

Participants in the experimental group will receive a structured 10-day rehabilitation program combining leg cycle ergometry with conventional physiotherapy. This protocol was modified from Faizan Hamid et al. [10] and Guida et al. (2020).

Initial sessions emphasize breathing control and gentle mobilization to promote circulation and respiratory efficiency. Leg cycle ergometry will begin on day 2 and increase gradually to 15 minutes by day 10, performed twice daily with continuous monitoring. Ambulation, chair transfers, and stepper training are progressively added to enhance lower-limb strength, venous return, and cardiorespiratory endurance. All ergometer sessions will be supervised by the same physiotherapist to ensure uniform progression and adherence.

### Control group

Participants in the control group will follow a 10-day progressive mobilization program based on standard Phase I cardiac rehabilitation [14, 15].

Sessions include diaphragmatic breathing, active limb mobility, chair transfers, stepper training, and ambulation, each performed twice daily for 10–15 minutes per session. Exercise progression will depend on patient tolerance and vital stability (SpO₂ ≥94%, HR ≤110 bpm, Borg RPE ≤13).

Sessions will be conducted under the same supervision and safety monitoring as the experimental group to ensure protocol fidelity.

#### Group A: experimental group (leg cycle ergometry + conventional physiotherapy)[16]

Participants will undergo a 10-day structured exercise program. Each session lasts 10–15 minutes, twice daily, continuously monitoring vital signs. Exercise progression is based on patient tolerance, as detailed in Table 1.

**Table 1 Tab1:** Day-wise structured protocol for Experimental Group

**Day**	**Exercise protocol**	**Patient position/rationale**
1	• Breathing exercises (1 set of 10 reps) • Active upper and lower limb mobility (1 set of 10 reps)	Supine, head of bed 45° – improve venous return and prevent orthostatic stress
2	• Breathing exercises (1 set of 10 reps) • Active upper and lower limb mobility (1 set of 10 reps) • Standing upright and on-the-spot walking (2 x 1 min) • Leg cycle ergometry (2min)	Supine for ergometer, supported standing for walk – early mobility, circulation
3	• Breathing exercises (1 set of 10 reps) • Active upper and lower limb mobility (1 set of 10 reps) • Standing upright and on-the-spot walking (2 x 1 min) • Ambulation around bed (2-3min) • Leg cycle ergometry(5min)	Edge of bed sitting for chair transfer, supine on ergometer to strengthen lower limbs and functional mobility
4	• Breathing exercises (1 set of 10 reps) • Active upper and lower limb mobility (1 set of 10 reps) • Standing upright and on-the-spot walking (2 x 1 min) • Ambulation around bed (2-3min) • Chair transfer (15min) • Leg cycle ergometry (5min)	Positions same as Day 3. Gradually increasing duration to improve endurance
5	• Breathing exercises (1 set of 10 reps) • Active upper and lower limb mobility (1 set of 10 reps) • Standing upright and on-the-spot walking (2 x 1 min) • Ambulation (15min) • Chair transfer (10-15min) • Leg cycle ergometry (10min)	Focus on progressive functional recovery
6	• Active mobility exercise • Ambulation (10-15min) • Step training on stepper (3–5 min x 2) • Leg cycle ergometry (10 min)	Standing/semi-standing for stepper, supine/seated for ergometer, to improve lower limb strength balance and cardiorespiratory fitness.
7	• Active mobility exercises • Ambulation (10–15 min) • Leg cycle ergometry (10min)	Maintain progressive intensity and endurance.
8	• Active mobility exercises • Stepper training (3–5 min x 2) • Leg cycle ergometry (15 min)	Resistance and ergometer exercise enhance muscle strength and functional capacity
9	• Active mobility exercises • Stepper training (3-5min x 2) • Leg cycle ergometry (15 min)	Resistance and ergometer exercise enhance muscle strength and functional capacity
10	• Active mobility exercise • Stepper training (3-5min x 2) • Leg cycle ergometry (15 min)	Resistance and ergometer exercise enhance muscle strength and functional capacity

#### Group B: control group (conventional physiotherapy)

Participants follow a 10-day progressive mobilization program without leg cycle ergometry. Exercise selection is based on published Phase I cardiac rehabilitation guidelines detailed in Table 2. (Supplementary 2).

**Table 2. Tab2:** Day-wise structured protocol for Control Group

Day	Exercise Protocol	Patient Position/Rationale
1	• Diaphragmatic breathing (1 set of 10 reps) • Active upper and lower limb mobility (1 set of 10 reps)	Supine, head-of-bed elevated 45° improve circulation, respiratory function
2	• Diaphragmatic breathing (1 set of 10 reps) • Active upper and lower limb mobility (1 set of 10 reps) • Standing upright and on-the-spot walking (2 x 1 min)	Standing with support; early ambulation promotes functional recovery
3	• Diaphragmatic breathing (1 set of 10 reps) • Active upper and lower limb mobility (1 set of 10 reps) • Standing upright and on-the-spot walking (2 x 1 min) • Ambulation around the ward (5 min) • Chair transfer (2 min)	Edge-of-bed sitting, standing for ambulation; improve independence
4	• Diaphragmatic breathing (1 set of 10 reps) • Active upper and lower limb mobility (1 set of 10 reps) • Standing upright and on-the-spot walking (2 x 1 min) • Ambulation around the ward (5 min) • Chair Transfer (5min)	Progressive increase in duration to enhance endurance
5	• Diaphragmatic breathing (1 set of 10 reps) • Active upper and lower limb mobility (1 set of 10 reps) • Standing upright and on-the-spot walking (2 x 1 min) • Ambulation (15 min) • Chair transfer (10 min)	Focus on functional mobility
6	• Active mobility exercises • Step training on the stepper (2 x daily) • Chair transfer (10 min)	Standing/semi-standing; improve lower limb strength and balance
7	• Active mobility exercise • Step training (2 x daily) • Chair transfer (15 min)	Maintain intensity and improve confidence in movement
8	• Active mobility exercises • Stepper training (2 x daily) • Resistance exercises (2 x 10 min)	Strengthening the lower limb and functional independence
9	• Active mobility exercise • Stepper training (2 x daily) • Resistance exercises (2 x 10 min)	Progressive overload for strength
10	• Active mobility exercises • Stepper training (2 x daily) • Resistance exercise (2 x 10 min)	Progressive overload for functional gains

Exercises will be paused or discontinued if any adverse symptoms appear, and patients will be re-evaluated before resuming activity.

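### Tables 1 and 2 do not share a common conventional programme, so if they are delivered as printed an effect cannot be attributed to ergometry alone

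*Protocol article*

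**What the plan says.** The Abstract's hypothesis, the Trial design section and both arm descriptions set up an add-on contrast. The Experimental group section describes a programme "combining leg cycle ergometry with conventional physiotherapy", and the text above Table 2 presents the control programme as one without ergometry. The Discussion counts uniform exercise protocols among its safeguards against bias, and says that confirmed benefits could make ergometry a routine part of Phase I care.

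The prose summarises the other content. For the experimental arm: "Ambulation, chair transfers, and stepper training are progressively added to enhance lower-limb strength". For the control arm: "chair transfers, stepper training, and ambulation, each performed twice daily for 10–15 minutes per session". Neither summary names resistance exercise.

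Tables 1 and 2 then give day-by-day schedules. Table 2 lists "Resistance exercises (2 x 10 min" on each of days 8 to 10; Table 1's exercise column lists no resistance work. Table 1 lists "Ambulation (10-15min" on day 6 and the same range on day 7; Table 2 lists no ambulation after day 5. On session length, Table 1's introduction says "Each session lasts 10–15 minutes, twice daily". Therapists work "using standardized checklists to ensure fidelity".

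**The concern.** An add-on trial isolates the added component only if everything else is the same by design. If the background programmes differ, randomisation still gives a fair comparison of the two packages as wholes, but it cannot say which part of a package produced a difference or concealed one.

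Two outcomes are most exposed. The co-primary 6-Minute Walk Test follows a schedule in which listed walking differs between arms. The secondary Manual Muscle Testing follows one in which resistance work is listed for controls only. No specific mechanism is claimed for the Vancouver Scar Scale. If the differences are only drafting errors, what is at stake is smaller: a published day-by-day protocol that cannot be followed or reported as the add-on it claims to be.

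**Working it through.** The protocol gives no figure to reproduce on this point. The check removes ergometry from Table 1 and compares what is left with Table 2. Days 1 and 2 match, apart from the naming of the breathing exercise.

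| Day | Experimental, ergometry removed | Control |
|---|---|---|
| 3 | ambulation 2–3 min; no chair transfer | ambulation 5 min; chair transfer 2 min |
| 4 | ambulation 2–3 min; chair transfer 15 min | ambulation 5 min; chair transfer 5 min |
| 5 | ambulation 15 min; chair transfer 10–15 min | ambulation 15 min; chair transfer 10 min |
| 6 | ambulation 10–15 min; stepper; no chair transfer | no ambulation; stepper; chair transfer 10 min |
| 7 | ambulation 10–15 min; no stepper; no chair transfer | no ambulation; stepper; chair transfer 15 min |
| 8–10 | stepper; no resistance | stepper; resistance 2 x 10 min |

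**Days that differ.** Counting overlapping ranges as equal: 3, 4, 6, 7, 8, 9, 10 = 7 days. Counting only a different set of components: 3, 6, 7, 8, 9, 10 = 6 days. Adding day 5 to the first count gives 8.

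**Listed minutes, each entry counted once per day.**
- Ambulation: experimental (2–3) + (2–3) + 15 + (10–15) + (10–15) = 39–51; control 5 + 5 + 15 = 25. Leaving out days 6 and 7: 19–21 against 25, so controls then have 4–6 min more.
- Chair transfer: experimental 15 + (10–15) = 25–30; control 2 + 5 + 10 + 10 + 15 = 42.
- Resistance: experimental 0; control 3 x 2 x 10 = 60. Ergometry on the same three days is 3 x 15 = 45, so as printed these days exchange one exercise for the other.
- Stepper: experimental 4 days x 2 x (3–5) = 24–40 min in 8 bouts; control 5 days x 2 = 10 bouts of unstated length. The arms are equal at 24/10 to 40/10 = 2.4–4.0 min per control bout, so the direction cannot be shown.

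**Reading in which Table 1 has lost items.** Its position and rationale column mentions chair transfer on day 3, and on days 8 to 10 says "Resistance and ergometer exercise enhance muscle strength and functional capacity". Neither item is in the exercise column. If both were left out by mistake, the component sets match on days 3 and 8 to 10, and the mismatch falls from 6 days to 2 (days 6 and 7). The resistance contrast may then vanish, while the duration differences in ambulation on day 3 and in ambulation and chair transfer on day 4 remain. If the word refers to pedal load (the Instrument description gives a manual resistance knob), the resistance contrast stands.

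**Session length.** Experimental day 5 lists 2 (on-the-spot walking) + 15 + (10–15) + 10 = 37–42 min before breathing and limb exercises. Two sessions of 10–15 min allow 20–30 min per day.

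**The case against.** The strongest case on the other side is that this is a drafting matter. The prose sections are summaries: components that are progressively added need not appear every day, and every component named for controls does appear in Table 2. That stands. A reader might infer that the tables flatly contradict the prose, but the conflict there is only partial: the Control group section names no resistance exercise, and its 10–15 min twice daily, if read for each component, does not fit table entries of 2 to 5 min. The main conflict lies elsewhere, between the promised common programme and a Table 1 that omits items listed in Table 2.

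It also stands that listed minutes are not delivered dose. Progression is by tolerance, and the day 5 entries exceed the stated session time. Tolerance governs pace, however; it does not explain resistance work scheduled in one arm only, or walking scheduled in the other only.

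Supplementary 2, cited beside Table 2, is not shown and may settle which schedule is right. The printed tables would still disagree with the stated contrast.

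Finally, a package comparison is a legitimate aim, and the Objectives and the end of the Introduction use comparative wording that would fit one. The hypothesis in the Abstract, though, concerns ergometry as an addition, and the Discussion's conditional conclusion concerns ergometry by name.

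**Conclusion.** The mismatch is certain as text: 7 of 10 days differ once ergometry is removed, 6 of them in components, or 2 in components if Table 1's rationale column reflects omitted items. The consequence is conditional: if the tables are delivered as printed, an effect, or its absence, on the 6-Minute Walk Test or Manual Muscle Testing cannot be attributed to ergometry alone.

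A reader might go further and infer that the trial is invalid, that the arms are known to receive different care, or that the bias runs in a known direction. The documents support none of these. The comparison of randomised packages holds. What is delivered is not stated beyond the conflicting text. The direction is open, since control-only resistance could mask a benefit, while the walking difference changes sign if controls walk the same amount as the experimental arm on days 6 and 7. Nothing in the protocol allows an effect on either outcome to be sized.

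**What to change.** Before any unblinded results are available, confirm with the treating therapists and the session checklists what is delivered in each arm. The logbooks are described as recording session adherence only, so they may not settle content.

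- **If the same conventional programme is delivered in both arms:** correct Tables 1 and 2 to show it, with ergometry as the only addition. Correct the 10–15 min session-length text as well, because it cannot hold the added ergometry. Which content is right is for the clinical team.
- **If delivery differs or is mixed, or checklists already in use carry the difference:** leave delivery unchanged. By protocol amendment and registry update, restate the hypothesis in the Abstract and the planned conclusion in the Discussion as a comparison of two rehabilitation packages, with no claim for ergometry alone.

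Aligning the arms now is not advised. Recruitment began in June 2025, and a change would mix two schedules within arms of 42.

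The cost is a document amendment to a protocol that stands at Version 1.0 with none so far and, in the second case, loss of the ergometry-alone claim. Neither route needs more patients or assessments.
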